#### Secondary outcomes (Part A only)

Secondary outcomes include a range of mental, cognitive and lifestyle outcomes and were collected at 6 weeks and 12 weeks post-randomisation.

##### Mental health status

Symptoms of poor mental health were assessed using the Depression Anxiety Stress Scale (DASS21) [57], the Short Warwick Edinburgh Mental Well-being Scale (SWEMWBS) [58], the Brief Psychiatric Rating Scale (BPRS) [59] and the brief insomnia severity index (ISI) [60]. The DASS21 is a 21-item questionnaire containing 3 subscales (depression, anxiety, stress) of 7 items, with possible scores ranging from 0 to 21. The subscales have high internal reliability in adults across a range of mental illnesses (Cronbach’s alpha of 0.94, 0.87 and 0.91 for depression, anxiety and stress, respectively) [61]. The SWEMWBS is a brief 7-item scale that measures key aspects of psychological functioning, scores range from 7 to 35, validated in people with SMI [58, 62]. The BPRS measures psychiatric symptoms including hallucinations, unusual thought content, emotional withdrawal, depression, anxiety and self-neglect [59] over 18-items, with total scores ranging from 18 to 126, with high inter-rater reliability and validity [63, 64]. The brief ISI is a 7-item questionnaire, with scores ranging from 0 to 28 whereby a score of 15 or above indicates clinical insomnia [60], validated for sleep disorders [60] and used previously in people with SMI [65–67].

##### Cognitive function

The Montreal Cognitive Assessment (MoCA) [68] is a brief screening tool that has high sensitivity and specificity for detecting mild cognitive impairments on a 0–30-point scale whereby a score below 26 indicates cognitive impairment [68].

##### Self-esteem

The Rosenberg Self-Esteem Scale (RSES) [69] measures self-esteem and global self-worth over 10 items, scores range from 0 to 30 [69]. The RSES has adequate internal consistency, test-retest reliability and construct validity in people with SMI [70, 71].

##### Lifestyle measures

The Short-Form International Physical Activity Questionnaire (IPAQ-SF) [72] captures self-reported physical activity and sedentary behaviour over 7 items and has been validated in people with SMI [73, 74] with comparable reliability and criterion validity to that reported in the general population [73, 74]. Motivation to engage in physical activity will be measured via The Behavioural Regulation in Exercise Questionnaire-3 (BREQ-3); it consists of 24 items related to six motivation types (amotivation, external regulation, introjected regulation, identified regulation, integrated regulation and intrinsic regulation) and has been validated in people with schizophrenia [75].

##### Cardiorespiratory fitness

The bicycle YMCA submaximal fitness test measures estimated VO2max [54]. This test provides an inexpensive, quick (15 min to administer) and safe measure of VO2max in comparison with maximal fitness tests which may provide more accurate findings but require the use of expensive or off-putting equipment (such as oxygen masks or mouthpieces) and highly skilled personnel [54]. Moreover, direct measurement requires participations to exercise until exhaustion, which may be challenging for those with lower baseline fitness and those with chronic psychiatric symptoms. The YMCA test has been validated for the prediction of VO2max [54] and has been used to predict VO2max in people with SMI [76, 77]. Additionally, gait speed was measured as the time taken to walk 6 m. Gait speed has been measured using similar estimates in previous studies with people with SMI [78, 79].

##### Anthropometric measures and cigarette intake

BMI, waist circumference (WC), blood pressure and cigarette intake were collected as they provide an indication of cardiometabolic and cardiovascular disease risk [80, 81]. WC was taken from the umbilicus with the participant standing. BMI was calculated based on height and weight. Systolic and diastolic blood pressure were collected via a blood pressure monitor using standardized techniques, two readings were taken at 5-min intervals and the second was used. Participants were asked about their daily cigarette intake.

#### Tertiary outcomes (Part A only)

The SEES assesses psychological states, and it has been validated to assess the effects of exercise on psychological states [56]. This self-report questionnaire contains 12 items, rated on a 7-point Likert scale, subdivided into three subscales to assess immediate feelings of positive well-being, psychological distress and fatigue.

Smokers were asked to rate cigarette craving on a 10-point Likert scale, with higher scores indicating higher levels of cravings. All participants rated appetite craving on a 10-point Likert scale and were additionally asked ‘If you do feel like eating what would it be?’.

### Data management

Each participant is being allocated an anonymised patient identification number (PIN). All information collected will be kept confidential; all identifiable data will be stored in locked filing cabinets. The outcome data is being collected on paper forms and will be transferred to an IBM Statistical Package for the Social Sciences (SPSS) database (SPSS version 27, Chicago, IL, USA). The research ethics committee will be consulted prior to any changes in protocol. The protocol used will be made available on request.

### Safety

During Part A, all AEs and adverse reactions (ARs) (any untoward and unintended response in a subject to a therapy which is related to any duration of therapy administered to that subject), whether serious or not, were to be reported to the ward-based clinical team within 24 h. Serious AEs (SAE), serious ARs (SAR) and unexpected serious ARs (USAR) were to be reported to the participant’s GP. Appropriate action was to be taken including (1) withdrawing the participant from the trial, (2) adapting the exercise regime for the participant (and potentially for other participants) and (3) terminating the trial if necessary.

SAEs, SARs and USARs are defined as any AE, AE or unexpected AR, respectively, that are life-threatening; require hospitalisation or prolongation of existing hospitalisation; or result in significant disability.

During Part B, if an AE or AR occurs during exercise, the session will be stopped and a physical health check will be carried out if required. The clinical team will be consulted. Depending on the severity of the event, the exercise regime may be adapted for that patient or it may be decided that they are not able to exercise at their current physical health status.

### Data analysis

Acceptability and feasibility outcomes will be reported post-randomisation and summarised by treatment arm (HIIT and TAU) and study phase (RCT and naturalistic phase). Descriptive statistics including percentages and raw figures will be used to assess feasibility outcomes and acceptability survey responses. All AEs will be listed. Satisfaction scores (a measure of acceptability) will be collated to form a mean satisfaction rating.

Data analysis, for secondary and tertiary measures, will be simplified to account for small sample size owing to suspension of the RCT in line with COVID-19-inflicted restrictions. Data analysis plan suggested a formal statistical analysis whereby secondary outcome variables measured at the intervention time points (6 and 12 weeks) were to feature as dependent variables with, treatment arm (HIIT or TAU), time (6 or 12 weeks), baseline BPRS, baseline fitness and baseline anthropometric measurements included as covariates.

In lieu of the above plan, to evaluate effectiveness of the intervention in line with our secondary aim, changes pre- and post-intervention in mental and physical parameters will be assessed, and Cohen’s *d* and confidence intervals will be calculated to determine between-group effect size for mean change. This secondary analysis will be based on the intention-to-treat sample.

Similarly, for the tertiary outcomes, changes pre- and post-intervention in psychological wellbeing, psychological distress, fatigue and appetite and cigarette cravings following a single bout of HIIT will be assessed, and Cohen’s *d* and confidence intervals will be calculated to determine between-group effect size for mean change. As above, this analysis will be based on the intention-to-treat sample. An additional analysis will be conducted with those participants who adhered to the HIIT protocol (completed the full 19-min HIIT session and who reached the target heart rate).

Data analysis will be conducted using Statistical Package for the Social Sciences (SPSS) version 27 (Chicago, IL, USA).

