**Fig. 3 Fig3:**
[figure not shown]
Schedule of enrolment, interventions and assessments in RCT

The RCT element of the study was suspended and then adapted due to the COVID-19 pandemic and the pausing of research projects. The naturalistic study is currently being undertaken to address issues surrounding the small sample size following the early termination of the RCT. There are currently no plans to resume recruitment in the RCT capacity. Specifically, a naturalistic design is being undertaken, rather than continuing with the original RCT format, due to the suspected difficulties in recruiting enough participants to fulfil both HIIT and TAU arms in the RCT design during covid. New admissions to inpatient wards dropped during the first wave of the pandemic, with an additional 2441 patients discharged from the hospital setting to free up bed capacity for the emergency response and to reduce the risk of infection [50]. This means that there were fewer inpatients with SMI overall, with many of those remaining in inpatient settings experiencing a greater symptom load, a more negative impact on functioning with attendant reduced likelihood and capacity of consenting to research and completing research assessments. The adapted naturalistic design will allow for the collection of feasibility and acceptability data which are the primary outcomes of the pilot study. Moreover, those who are more severely ill are less likely to participate in RCTs of lifestyle interventions [51]; thus, the use of a naturalistic design may provide a greater indication of uptake of HIIT in a clinical capacity.

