### Participants

Participants are being recruited from adult inpatient settings operating in SLaM, through adverts and presentations at ward-based community meetings for patients and via clinician referral. Additionally, posters are being displayed onwards with a request that anyone with an interest in taking part should contact the research team. All those who display an interest will be given written information on the study and invited to take part, providing they meet study eligibility criteria.

Individuals are eligible for the study if they meet the following criteria: (1) a service user receiving inpatient care in the participating NHS Trust for a severe mental health condition (including schizophrenia, MDD and bipolar disorder), (2) sufficient command of spoken English, and (3) able to provide written informed consent. Exclusion criteria include (1) a medical condition that impedes exercise (e.g., chronic back pain), (2) an eating disorder (e.g., anorexia nervosa, bulimia nervosa) characterised by excessive exercise, and (3) pregnancy. Additionally, in Part A of the research design eligibility was limited to those aged 18–60 years old.

We aimed to recruit 40 participants to the RCT phase, 20 in the intervention and 20 in the control group over a 1-year period. This number is based on recruiting a big-enough sample to assess the feasibility of the study and on the resources available [52]. We aim to recruit 10 participants to the naturalistic phase of the study. This reduced sample considers COVID-19-related challenges to recruitment, including reduced referrals and admissions to inpatient mental health wards during the pandemic [50].

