### Criteria to indicate that a future effectiveness trial is feasible

At present, no large-scale study is planned; however, feasibility outcomes will provide an indication as to whether a future effectiveness trial is warranted [48]. Criteria that indicate that a future effectiveness trial is feasible include (1) a majority of wards agreeing to hosting the project, (2) meeting stated recruitment (40 participants to the RCT and 10 participants to the naturalistic study phase), (3) comparable completion rates and adherence to other exercise interventions carried out in people with SMI (drop-out rates of previous exercise interventions in people with SMI has averaged 24–32.5% and adherence to scheduled sessions has averaged 55–94% [41, 42, 83], (4) lack of serious exercise-related AEs and (5) participants expressing that the conduct of the intervention was acceptable.

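### The primary feasibility proportions and the serious-event criterion are read against benchmarks without stated precision, which is very low at the Part B target of 10

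*Protocol article*

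**What the plan says.** The Data analysis section of the protocol article sets out the analysis of the primary outcomes: "Descriptive statistics including percentages and raw figures will be used to assess feasibility outcomes and acceptability survey responses". Adverse events are to be listed, and satisfaction scores averaged. Results are to be "summarised by treatment arm (HIIT and TAU) and study phase (RCT and naturalistic phase"). For the secondary and, again, the tertiary outcomes, the same section adds Cohen's d and says that "confidence intervals will be calculated to determine between-group effect size for mean change".

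The section on criteria for a future effectiveness trial uses the primary figures. Completion and adherence should be comparable with earlier exercise studies, for which it reports that "drop-out rates of previous exercise interventions in people with SMI has averaged 24–32.5" per cent. A separate criterion is "lack of serious exercise-related AEs". No interval or allowance for chance is attached to either.

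On numbers, the Participants section says "We aimed to recruit 40 participants to the RCT phase, 20 in the intervention and 20 in the control group over a 1-year period", and then "We aim to recruit 10 participants to the naturalistic phase of the study". The abstract gives 6–8 for the naturalistic phase. The RCT stopped early. The Design section says that the naturalistic study is meant to "address issues surrounding the small sample size following the early termination of the RCT", but the number actually randomised is not given.

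**The concern.** The outcomes that answer the primary aim are the only ones for which the plan describes no measure of precision, although they rest on the smallest numbers. The lower-ranked outcomes do get intervals. The Discussion shows the same imbalance: it says that the suspension limits power for the secondary and tertiary outcomes, and does not mention the precision of the primary ones.

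Two things are at stake. A completion percentage from about 10 people may be called comparable, or not comparable, with earlier studies when the data can hardly tell the two apart. And a count of zero serious exercise-related events may carry more weight in the feasibility judgement than so few participants can support.

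**Working it through.** **The plan's own figure.** The targets of 40 and 10 are justified by feasibility and resources, with no precision, error rate or power input. There is no calculation to reproduce, so the check is of the precision these numbers give.

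**Inputs from the documents.** Part B target 10 (Participants; also the criteria section) or 6–8 (Abstract). Planned RCT HIIT arm 20 (Participants). Drop-out benchmark 24–32.5% (criteria section), which is completion of 67.5–76%.

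**Assumptions made here.** 95% exact intervals. Illustrative true drop-out rates of 24–50% and true serious-event risks of 5–20% per participant. For the pooled figure, all planned participants reach HIIT: 20 + 10 = 30.

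**Step 1: precision of a drop-out proportion.** For x events in n, the Clopper–Pearson limits are the 2.5% quantile of Beta(x, n−x+1) and the 97.5% quantile of Beta(x+1, n−x).

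| Setting | Drop-outs | Exact 95% CI |
|---|---|---|
| Part B, n = 6 | 2/6 = 33% | 4.3–77.7% |
| Part B, n = 8 | 2/8 = 25% | 3.2–65.1% |
| Part B, n = 10 | 3/10 = 30% | 6.7–65.2% |
| Planned HIIT arm, n = 20 | 6/20 = 30% | 11.9–54.3% |

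**Step 2: how often an observed drop-out no higher than 32.5% would occur.** At n = 10 this means 3 or fewer drop-outs, so the probability is P(X ≤ 3) with X ~ Binomial(10, p).

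| True drop-out p (assumed) | P(X ≤ 3 of 10) |
|---|---|
| 24% | 0.80 |
| 28% | 0.70 |
| 40% | 0.38 |
| 45% | 0.27 |
| 50% | 0.17 |

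A true rate at the favourable end of the benchmark (24%) would exceed 32.5% in the sample 20% of the time. A true rate of 40% would look acceptable 38% of the time. At n = 20 (6 or fewer drop-outs) the corresponding figures are 18% and 25%.

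**Step 3: zero serious exercise-related events.** The upper 95% limit is 1 − 0.05^(1/n) one-sided and 1 − 0.025^(1/n) two-sided. For n = 10, 1 − 0.05^(0.1) = 0.259 and 1 − 0.025^(0.1) = 0.308. The chance of seeing no event at true risk p is (1 − p)^n.

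| n | Upper limit, one-sided | Upper limit, two-sided | P(0 events), p = 5% | p = 10% | p = 20% |
|---|---|---|---|---|---|
| 6 | 39.3% | 45.9% | 0.74 | 0.53 | 0.26 |
| 8 | 31.2% | 36.9% | 0.66 | 0.43 | 0.17 |
| 10 | 25.9% | 30.8% | 0.60 | 0.35 | 0.11 |
| 20 | 13.9% | 16.8% | 0.36 | 0.12 | 0.01 |
| 30 | 9.5% | 11.6% | 0.22 | 0.04 | 0.001 |

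The row for 30 is the best case at the planned numbers. The RCT ended early, and Part B participants may choose self-directed sessions instead of HIIT, so the number exposed could be well below 30.

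**The case against.** The strongest reply is that this is a descriptive pilot reported in a journal article. Whether a proportion carries an interval is often settled in an analysis plan, and the wording on descriptive statistics does not exclude one. Raw figures will be shown and all adverse events listed, so a reader can derive the intervals. That is fair, and it rules out saying that the imprecision would be hidden. It does not remove the point: the article does specify intervals, but only for the lower-ranked outcomes, and it sets the primary figures against benchmarks.

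Several stronger readings are tempting, and the documents do not support them:

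- **That each phase has about 10 participants.** Ten is the Part B target only. The RCT target was 40, and the achieved number is not stated.
- **That a formal go decision could be wrong by chance.** The criteria section says that no large trial is planned and that the outcomes give an indication. It does not say how the criteria combine, and one of them is recruiting 40 to an RCT with no plans to resume. There is no decision rule whose error rate could be calculated.
- **That drop-out must fall inside 24–32.5%, so that only 3 of 10 would do.** The range describes earlier studies and the test is comparability. Nothing suggests that lower drop-out would count against feasibility.
- **That zero events would be taken as proof of safety.** The criterion concerns events, and the article nowhere says that their absence establishes safety.

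It is also fair to say that Part B suits a drop-out benchmark poorly. It has no time limit, allows reduced participation and does not invite discharged patients back. The Part B drop-out interval therefore illustrates precision at n = 10. The zero-event limits do not need a fixed course, but they do depend on the number exposed.

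**Conclusion.** The point holds as a moderate weakness in how the primary results are to be analysed and interpreted. No stated figure is wrong. As written, the primary feasibility proportions are assessed without intervals and compared with benchmarks, while intervals are reserved for secondary and tertiary outcomes. At the Part B target of 10, 3/10 drop-outs is compatible with a true rate of 7–65%, and 0/10 serious events with a risk of up to 26% (one-sided) or 31% (two-sided). At the abstract's 6–8 the precision is worse. Pooling the planned 30 HIIT participants brings the one-sided limit to about 9.5%, on the unverified assumption that all 30 were recruited and exposed. The conclusion about low precision in Part B rests only on the stated targets and exact binomial limits. The probabilities of meeting a benchmark rest on assumed true rates.

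**What to change.** Four changes to the Data analysis and criteria sections:

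1. Report ward uptake, completion and serious exercise-related adverse events with exact (Clopper–Pearson) 95% confidence intervals by phase. For adverse events, add the interval for all HIIT-exposed participants, using the numbers actually exposed. Session attendance is clustered within participants, so a simple binomial interval on sessions would not suit it.
2. State the drop-out benchmark one-sided (not above 32.5%), show its interval, and apply it mainly to Part A, because Part B has no fixed course to complete.
3. Word the safety criterion as no serious exercise-related adverse event observed, with the upper 95% limit reported, and say whether that limit is one- or two-sided.
4. Present the overall feasibility judgement as indicative within those limits.

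The cost is a few lines of analysis and wording, and a less firm conclusion. No extra patients or data are needed. Feasibility is to be assessed after both phases finish, and Part B was still recruiting at publication, so the change could be made before that assessment.

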### Aims

The primary aim of this feasibility study therefore is to determine whether HIIT is acceptable and feasible to implement in a psychiatric inpatient setting with patients with a broad range of severe mental illnesses, while the secondary aim is to investigate if the HIIT intervention improves mental health symptoms, including psychiatric symptoms, depression, anxiety, stress, sleep and mental wellbeing; cognition; and along with physical activity measures including increases in weekly physical activity, motivation to engage in exercise and anthropometric measures. The tertiary aim is to determine whether a single bout of HIIT leads to acute changes in psychological states and appetite and cigarette cravings. Conclusions drawn from our secondary and tertiary aims will offer an indication of the therapeutic benefits of HIIT in preparation for larger scale work.

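### Cohen's d is adopted because the sample is small, yet in small samples it overstates effect size; Hedges' g and a difference in scale units would serve better

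*Protocol article*

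**What the plan says.** The Data analysis section describes a model for the week 6 and week 12 outcomes with arm, time and "baseline BPRS, baseline fitness and baseline anthropometric measurements included as covariates". It then withdraws that model: "Data analysis, for secondary and tertiary measures, will be simplified to account for small sample size", the cause being suspension of the RCT. The replacement is introduced with "In lieu of the above plan, to evaluate effectiveness of the intervention in line with our secondary aim". Pre-to-post changes are to be assessed, and Cohen's d and "confidence intervals will be calculated to determine between-group effect size for mean change". The same measure is prescribed for the single-bout tertiary outcomes. No small-sample correction is named.

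Under Aims, the purpose of these results is given as: "Conclusions drawn from our secondary and tertiary aims will offer an indication of the therapeutic benefits of HIIT in preparation for larger scale work".

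On size, the Participants section states: "We aimed to recruit 40 participants to the RCT phase, 20 in the intervention and 20 in the control group over a 1-year period". The basis is feasibility and resources. The Design section puts RCT recruitment between January and March 2020, and the text below Fig. 3 says there are no plans to resume it. The number actually randomised is not reported.

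**The concern.** The document gives few participants as the reason for using Cohen's d, and few participants is the condition in which d is biased. The pooled SD in its denominator is estimated with few degrees of freedom, and on average this makes the ratio too large in absolute value. The bias is proportional to the true effect and vanishes when there is none.

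A second, smaller matter is the use of change scores. Subtracting the baseline amounts to assuming a slope of 1 between baseline and follow-up. If the true slope is lower, part of any chance baseline difference between arms stays in the estimate.

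These effect sizes are the study's only between-group indication of benefit, because the naturalistic phase does not measure these outcomes. Whoever reads them as an indication for later work should have an estimate without an avoidable bias, on a scale that can be interpreted.

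**Working it through.** **Inputs from the protocol article.** Planned 40 over one year, allocated 1:1 (Participants; RCT design: Part A). Recruitment open January to March 2020 (Design). The target of 40 rests on feasibility and resources ("This number is based on recruiting a big-enough sample to assess the feasibility of the study and on the resources available"), with no alpha, power or SD, so there is no statistical figure to reproduce.

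**Assumptions.** At the planned rate, 40/12 = 3.3 per month, two to three months give about 7 to 10 participants. The baseline–follow-up correlation r is not given, so 0.5 and 0.7 are used, with equal SDs at both times.

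**1. Bias of d.** With df = N − 2, J = Γ(df/2) / [√(df/2) Γ((df − 1)/2)], and the expected overstatement is 1/J − 1.

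| N | J | Overstatement |
|---|---|---|
| 40 | 0.980 | 2.0% |
| 20 | 0.958 | 4.4% |
| 10 | 0.903 | 10.8% |
| 8 | 0.869 | 15.1% |
| 6 | 0.798 | 25.3% |

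An observed d of 0.50 at N = 10 becomes g = 0.903 × 0.50 = 0.45.

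**2. Imprecision, for comparison.** The noncentral-t 95% interval for an observed d of 0.5 is −0.78 to 1.75 at N = 10 and −0.13 to 1.13 at N = 40.

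**3. Standardiser.** Dividing by the SD of change instead of the baseline SD multiplies d by 1/√(2(1 − r)): 1.00 at r = 0.5, 1.29 at r = 0.7 and 1.58 at r = 0.8.

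**4. Chance imbalance.** A baseline difference B shifts the change-score contrast by −(1 − r)B. The SD of B is √(2/n), with n per arm. At n = 5 this is 0.63 SD, so the resulting error has an SD of 0.5 × 0.63 = 0.32 at r = 0.5 and 0.3 × 0.63 = 0.19 at r = 0.7. At n = 20 the figures are 0.16 and 0.09. The sign depends on B. With a true effect of 0.5 and r = 0.5, B = +0.5 gives 0.5 − 0.25 = 0.25, and B = −0.5 gives 0.75. In simulation (40,000 trials per setting) the unadjusted change contrast averaged 0.49 to 0.51 over all randomisations, so it is unbiased overall.

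**5. What adjustment buys.** The variance ratio of ANCOVA with one covariate to the change score is [(1 + r)/2] × [1 + 1/(N − 4)]. The interval-width ratio is its square root times t(N − 3)/t(N − 2), using 97.5% points.

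| N | r = 0.5 | r = 0.7 |
|---|---|---|
| 10 | √0.875 × 2.365/2.306 = 0.96 | √0.992 × 1.025 = 1.02 |
| 8 | √0.938 × 2.571/2.447 = 1.02 | √1.063 × 1.051 = 1.08 |
| 6 | √1.125 × 3.182/2.776 = 1.22 | √1.275 × 1.146 = 1.29 |

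At r = 0.9, which is conceivable for scores taken either side of a 19-minute session, the ratio at N = 10 is √(0.95 × 7/6) × 1.025 = 1.08.

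**The case against.** Four points can be made for the plan.

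- **The bias is small beside the uncertainty.** Moving from 0.50 to 0.45 matters little within an interval of −0.78 to 1.75, and the plan already commits to confidence intervals. This stands, and it limits the weight of the point. The correction still costs nothing.
- **The size is unknown.** The 11% and 15% figures depend on an assumed recruitment rate. At the only stated size, 40, the bias is 2.0%. This stands, so the result is a range.
- **Such details belong in an analysis plan.** This is fair for the standardiser and the interval method. It is not an answer on the measure itself, because the article names Cohen's d as the replacement.
- **Dropping the multi-covariate model was reasonable.** This also stands. That model would have strained so small a sample.

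A reader might go further and infer that baselines are ignored, that imbalance inflates the effects, and that the next trial would therefore be too small. The document does not support this. Every baseline is used, by subtraction. Imbalance acts in either direction, the change-score contrast is unbiased over randomisations, and its interval already covers that error. The section on criteria for a future effectiveness trial says no large-scale study is currently planned, and none of its five criteria uses an effect size.

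**Conclusion.** The point holds as a modest improvement to a stated method. Cohen's d overstates magnitude by an expected 2.0% at N = 40, about 11% at N = 10 and 15% at N = 8; the last two sizes assume recruitment at the planned rate. Only this part is systematic overstatement.

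The fixed slope of 1 is a secondary matter of efficiency and of conditional error. Whether adjustment helps depends on the analysed N and on r, neither of which the document gives. It is not clearly better at N = 10 and is worse at N = 8 and N = 6 over the correlations examined. The finding concerns secondary and tertiary outcomes only and leaves the primary feasibility and acceptability conclusions as they are.

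**What to change.** - For each secondary and tertiary outcome, report the between-group difference in mean change in the units of the scale, with a t-based 95% confidence interval, as the main result.
- Replace Cohen's d with Hedges' g (J × d) and state the standardiser. With the SD of change, a noncentral-t interval applies directly. With the baseline SD, the interval also depends on r, so the scale-unit interval should carry the inference.
- State the number analysed per arm beside each estimate.
- Where about 10 or more participants are analysed, consider regressing follow-up on arm and the outcome's own baseline, with no other covariate. Below that, the change-score difference may be kept. The same holds for the single-bout scores if their pre/post correlation is high. Fix the rule before looking at results by arm.

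No new data are needed. Hedges' g takes one multiplication per outcome and makes the reported values slightly smaller. Adjustment costs one degree of freedom: at N = 10 the interval is about 4% narrower at r = 0.5 and 2% wider at r = 0.7.
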